## Abstract

**Introduction:** Relapse is very common in drug abusers and contributes to a series of negative consequences. Effective addiction treatment exists but there are some problems in the implementation process. Mobile health (mHealth) offers a potential solution to improving recovery outcome for drug abusers in the community. The research team developed a community-based addiction rehabilitation electronic system (CAREs). The primary aim of this study is to explore whether the integrated rehabilitation based on program CAREs promotes drug abusers to keep abstinence. The secondary aim is to evaluate the impact of CAREs on interaction between drug users and service providers, and on addiction-related physical and social functions.

**Method and analysis:** A randomized controlled trial (RCT) will be conducted. The study is a superiority trial with parallel group design. Seventy drug abusers who are newly ordered to undergo community rehabilitation will be recruited from the community in Shanghai. Participants will be 1:1 randomly assigned to receive integrated community rehabilitation by using CAREs or only receiving routine community rehabilitation for 6 months. Corresponding social workers will provide service and monitor their drug use behavior in accordance with the routine work-flow. Outcomes will be assessed at baseline and in the 6th month. The primary outcome is the performance on illicit drug urine test which will be carried out regularly twice per week during the study period. Secondary study outcomes include longest duration of sustained abstinence, days that participants interact with social workers, and the decrease rate of addiction-related issues severity index. Chi-square tests and ANOVAs will be used to compare characteristics of the members of the two groups. GEE will be used to compare the seven dimensions scores of the ASI between groups.

**Discussion:** The study provides evidence for the feasibility and effectiveness of the “CAREs” system through comparing the results of the intervention group with the control group. This paper describes the design and methodology of the study.

**Ethics and dissemination:** The Ethical Board of SMHC approved the study protocol. All participants will present for the informed consent process. After study completion, the results will be published.

**Trial Registration:** ClinicalTrials.gov NCT03451344, https://clinicaltrials.gov/ct2/show/NCT03451344

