### Study setting

The setting for this study is in Shanghai, China. According to the Anti-Drug Law which was issued in 2007, drug abusers discharged from compulsory treatment programs should receive community-based rehabilitation for around 2 years. In Shanghai, community social workers in the addiction recovery services are employed by the government to help drug users and monitor their drug use behavior. There are around 1,000 social workers serving about 70,000 drug users in Shanghai.

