### Outcomes

The primary outcome is the performance on urine drug screen (UDS) which will be carried out regularly during the study period twice per week. The results of urine tests will be examined in the difference of proportion of drug-positive samples between two groups. Urine test kit will be used to test drug use including heroin, amphetamine-type stimulants, marijuana, cocaine, and ketamine. A subject who does not submit urine samples during the intervention period or who refuses to submit a sample even if he/she is present at the site will be considered as having a positive UDS.

Secondary outcomes include: (a) longest duration of sustained abstinence, defined as the longest continuous record weeks of negative urine drug screen samples; (b) interaction with social workers in the addiction recovery services: the days that participants interact with their corresponding social workers will be collected during the study period. Any phone call, SMS, face-to-face meeting, or communication via CAREs will be considered as one interaction; (c) the decrease rate of addiction-related issues severity index: the Chinese translation of the Addiction Severity Index (ASI) that has good reliability and validity in China will be used to assess the severity of addiction at enrollment and 6 months after enrollment. The reliability and validity of the Chinese version of the instrument have been assessed (21, 22). The internal consistency of the seven dimensions was judged to be acceptable (alpha = 0.44~0.79), the test-retest reliability was good (ICC = 0.68~0.84), and the inter-rater reliability was good (ICC = 0.87~0.98). The descent rate will be counted via dividing the minus value between baseline score and 6 months score by baseline score (assessments completed at assessment phases shown in Table 3).

**Table 3 T3:** Assessments completed at assessment phases.

**Assessments**		**Assessment Phase**		
		**T1**	**T2**	**T3**

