### Participant timeline

Individuals who express interest will be invited to participate in informed consent procedures. Those who voluntarily consent to participate will then enter a 3 days screening to determine whether they meet inclusion/exclusion eligibility criteria. Baseline measurements of drug use and UDS will also be collected at this time. Participants who continue to meet eligibility criteria will participate in a 7 days induction period. During the induction period, participants and their corresponding social workers will be trained by technicians to get familiar with CAREs. Participants will be randomly assigned, in a 1:1 ratio, to receive either the intervention program or control program for a period of 6 months. Subsequent assessment points coincide for both groups at 6 months after randomization (see Figure 4).

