### Data management

Intention-to-treat principle will be used in the statistical analysis. All statistical analyses will be conducted using SPSS Statistics (version 22) (24). Chi-square tests and ANOVAs will be used to compare characteristics of the members of the two groups. Primary outcome and secondary outcomes (results of urine illicit drug tests between the groups, the days that participants interact with their corresponding social workers) will be compared between groups using analysis of ANOVAs. Considering behavioral clinical trials often find data missing at the end of trials due to incomplete evaluations, Generalized Estimating Equations (GEE) will be used to compare the seven dimensions scores of the ASI between group across the study period. Any unfavorable changes to participants during the study period will be recorded. Since this study does not impact participants' routine care and is examining the effect of an integrated community-based rehabilitation for drug abusers in communities, no serious adverse events are anticipated and no interim analyses are planned.

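### The ASI secondary outcome is declared as a fall relative to baseline, which fails at a zero baseline and is not the quantity that the stated GEE analyses

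*Protocol article*

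**What the plan says.** Outcomes names secondary outcome (c) as "the decrease rate of addiction-related issues severity index" and gives its formula: "The descent rate will be counted via dividing the minus value between baseline score and 6 months score by baseline score". The same section places the ASI at enrolment and at 6 months. It gives no rule for a baseline of zero and does not say whether the rate is computed for each dimension or for a total. The Abstract and Table 3 also name the outcome as a decrease rate.

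The analysis is stated twice, and both times on a different quantity. The Abstract says "GEE will be used to compare the seven dimensions scores of the ASI between groups". Data management says "Generalized Estimating Equations (GEE) will be used to compare the seven dimensions scores of the ASI between group across the study period". The ANOVA sentence in Data management mentions secondary outcomes in general, but its parenthesis lists only the urine results and the days of interaction with social workers.

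On the schedule, Table 3 marks only drug use and the urine drug screen at T1, and marks the ASI decrease rate at T3 only. Participant timeline says "Baseline measurements of drug use and UDS will also be collected at this time" and does not mention the ASI.

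**The concern.** There are two linked problems.

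- **The formula.** Dividing by the participant's own baseline gives no value at zero and very large values near zero. Anyone who starts at zero in a dimension cannot be scored, whether they stay at zero or get worse.
- **The mismatch.** The declared outcome is a ratio, while the stated analysis is of scores. A reader cannot tell which one the trial will report as its ASI result. If the two disagree, either could be put forward afterwards, and the plan has no text to settle it.

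The schedule adds a smaller ambiguity. The baseline ASI is needed as the denominator of the ratio and for any baseline-adjusted comparison of scores, yet neither place that lists baseline measurements includes it. A baseline assessment that is missed cannot be recovered later.

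**Working it through.** The plan states no figure for this outcome, so there is nothing to reproduce. The check has three parts.

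**1. Behaviour of the formula.** Let B be the baseline score and F the 6-month score. From Outcomes, r = (B - F)/B. The article gives no ASI score range or distribution, so every score below is invented for illustration.

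| B | F | B - F | r |
|---|---|---|---|
| 0 | 0 | 0 | undefined |
| 0 | 0.20 | -0.20 | undefined |
| 0.02 | 0.04 | -0.02 | -100% |
| 0.02 | 0 | 0.02 | +100% |
| 0.50 | 0.40 | 0.10 | +20% |

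A change of 0.02 from a small baseline gives a rate of 100% in either direction. A change five times as large (0.10) from a baseline of 0.50 gives 20%.

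**2. Rate against score.** Take three participants with (B, F) = (0.05, 0.20), (0.60, 0.30) and (0.40, 0.20).

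- Falls in score: -0.15, 0.30, 0.20. Mean = 0.35/3 = 0.117, an improvement.
- Rates: -0.15/0.05 = -300%, 0.30/0.60 = +50%, 0.20/0.40 = +50%. Mean = -200%/3 = -67%, a worsening.

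The same data lead to opposite conclusions. The example shows that this can happen, not that it will happen in this trial.

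Setting the texts side by side, Outcomes declares r. The Abstract and Data management model the dimension scores. The ANOVA parenthesis does not list r. No named analysis therefore uses the declared quantity. If the general mention of secondary outcomes in the ANOVA sentence were read to include r, the ASI would have two analyses and no rule for which one counts.

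**3. How many ratios could be undefined.** Sample size gives 35 per group, 70 in all. If a share q of baselines in a dimension is zero, the expected number of undefined ratios in that dimension is 70q:

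| q (assumed) | 70q |
|---|---|
| 0% | 0 |
| 5% | 3.5 |
| 10% | 7 |
| 20% | 14 |

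The document does not support any particular q, including a q above zero. These losses arise only if r itself is analysed. The month-6 score, or the change in score, is defined whatever the baseline.

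**The case against.** The strongest reply is that the planned GEE works on scores. It keeps participants with a zero baseline, and near-zero denominators cannot dominate it. A reader might infer from the formula that participants who relapse from a zero baseline will vanish from the analysis and that harm will be hidden. The stated analysis does not do that. The primary outcome also measures drug use directly, with missed urine samples counted as positive. This reply stands: the loss and instability apply only if the declared rate is itself analysed. It does not remove the mismatch, because the rate remains the declared outcome.

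A reader might also infer that zero baselines are common, since Study setting describes people who come from compulsory programmes: "drug abusers discharged from compulsory treatment programs should receive community-based rehabilitation for around 2 years". The documents do not support this. They give no ASI distribution, and Eligibility criteria requires participants to meet DSM-5 criteria for substance dependence. If the rate were taken on a total, an exact zero would be less plausible still.

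On the schedule, Table 3 lists the derived rate, which can exist only at T3. Outcomes plainly plans the ASI at enrolment, and the list in Participant timeline is not worded as exhaustive. It would be wrong to conclude that no baseline ASI will be collected. What remains is a clarification.

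Finally, Data management justifies GEE with "Considering behavioral clinical trials often find data missing at the end of trials due to incomplete evaluations". A reader might go on to argue that unweighted GEE is invalid here because the missing participants are mostly relapsed or incarcerated. That composition is not stated: Discontinuation allows withdrawal for incarceration or readmission but lists other reasons too. A mixed model or ANCOVA would not cure missingness that depends on unseen relapse either. No finding is made on this.

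**Conclusion.** The point holds for the definition and its mismatch with the analysis. The declared ASI outcome is undefined at a zero baseline, unstable at small baselines, silent on dimension or total, and used by no named analysis. The failure at zero follows from the formula alone. The mismatch follows from the article's own text and is not a detail left to an unseen analysis plan. That the two measures can disagree in sign is shown by an invented example (+0.117 in mean score fall against -67% in mean rate). How often this would matter in the trial is unknown, because the share of zero or small baselines is not given.

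The weight is moderate. One of three secondary outcomes is affected and the primary outcome is not. The change should be made because it is nearly free and removes a choice that would otherwise be made after the data are seen. The schedule item is editorial.

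**What to change.** - In Outcomes, define the ASI outcome as the month-6 score in each of the seven dimensions.
- In Data management, state that arms are compared with adjustment for baseline: ANCOVA, or the arm-by-time term in the planned GEE or in a mixed model. The planned GEE need not be replaced. Report the adjusted difference with its 95% CI for each dimension.
- Drop the decrease rate, or keep it as descriptive only. If kept, say whether it is per dimension or on a total, and give a rule for a zero baseline.
- Bring the outcome's name in the Abstract and Table 3 into line.
- As a clarification, add the ASI to the T1 column of Table 3 and to the baseline measurements in Participant timeline, to agree with the enrolment ASI in Outcomes.

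The cost is wording and a table entry. No data are needed beyond the enrolment and 6-month ASI already planned.

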**BASELINE**				
	Drug use and UDS	X		
**PRIMARY OUTCOME**				
	The performance on UDS		X	X
**SECONDARY OUTCOMES**				
	Longest duration of sustained abstinence			X
	Interaction with social workers			X
	The decrease rate of addiction-related issues severity index			X

*T1: Baseline assessment*.

*T2: Duration of 6-month intervention*.

*T3: Completion of 6-month intervention*.

### Participant timeline

Individuals who express interest will be invited to participate in informed consent procedures. Those who voluntarily consent to participate will then enter a 3 days screening to determine whether they meet inclusion/exclusion eligibility criteria. Baseline measurements of drug use and UDS will also be collected at this time. Participants who continue to meet eligibility criteria will participate in a 7 days induction period. During the induction period, participants and their corresponding social workers will be trained by technicians to get familiar with CAREs. Participants will be randomly assigned, in a 1:1 ratio, to receive either the intervention program or control program for a period of 6 months. Subsequent assessment points coincide for both groups at 6 months after randomization (see Figure 4).

**Figure 4 F4:**
[figure not shown]
Participant flow diagrams.

### Discontinuation

The end of the study is defined as participants finishing the evaluation at the end of 6 months, or withdrawal from the study. Subjects are free to withdraw from the study at any time for any reason. They could also be withdrawn by the investigator, if necessary, to protect their health and the safety or integrity of the study data. The principal investigator could withdraw a participant from the study for any of the following reasons: (a) rehabilitation failure (having incarceration or readmission to compulsory treatment or both; (b) a protocol deviation that might compromise data integrity, protocol compliance or subject safety; (c) a participant's request to be discontinued from the study (i.e., a subject declines further study participation).

### Sample size

This is a pilot study design. Based on official records of the community-based rehabilitation program in Shanghai (23), the investigators estimated that the proportion of drug abusers in this program is around 40% and the proportion of loss-to-follow-up is 20%. Related literature pointed out that the use of mobile APP can result in a 60% reduction in substance use. Assuming α = 0.05, β = 0.10, a 70 participants sample size was calculated by sample size estimation for a comparison of two proportions. The sample size required for comparing the difference of performance on illicit drug urine test in two group (controlled group vs. integrated rehabilitation group) is 35 cases per group.

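### The 90% power claimed for 35 per arm leaves undefined the two rates compared and the role of the 20% loss, and is not shown to hold once non-submitters count as drug-positive

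*Protocol article*

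**What the plan says.** The Sample size section of the protocol article estimates from official programme records that "the proportion of drug abusers in this program is around 40% and the proportion of loss-to-follow-up is 20" per cent. It adds: "Related literature pointed out that the use of mobile APP can result in a 60% reduction in substance use". Then: "Assuming α = 0.05, β = 0.10, a 70 participants sample size was calculated", by "sample size estimation for a comparison of two proportions", which gives 35 per group. It does not print the two proportions, the sidedness of the test or the variance formula, and it does not say how the 20% was used.

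The Outcomes section defines the primary outcome as the proportion of drug-positive samples from twice-weekly testing. Its missing-data rule covers "A subject who does not submit urine samples during the intervention period", or who refuses a sample when present: that person is treated as having a positive screen, in either arm. The Data management section adds: "Intention-to-treat principle will be used in the statistical analysis". It names ANOVA for the primary comparison.

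**The concern.** Under these rules, people lost to follow-up do not leave the primary comparison. They stay in the denominator as positives. If a fraction d is lost in both arms, both rates rise and their difference shrinks by the factor (1 − d). A 60% reduction among people who are followed is then a smaller reduction on the endpoint as analysed. A conventional dropout allowance (dividing N by 0.8) corrects for fewer people but not for a smaller effect.

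The Sample size section does not show that its rates were set on this scale. If they were not, a non-significant result from 70 participants could be read as a negative finding with 90% power when the power was well below that. Correcting only the arithmetic from 40% and 60% would leave this problem in place.

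**Working it through.** **Inputs.** 40%, 20%, 60% reduction, α = 0.05, β = 0.10 and 35 per group come from Sample size; missing scored as positive from Outcomes; intention to treat from Data management. Sidedness and variance form are not stated, so both were tried.

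**Formulas** (v = p₁(1−p₁) + p₂(1−p₂); p̄ = mean of the two rates)
- Unpooled: n = (z_α + z_β)² v / (p₁−p₂)². Two-sided, (1.960 + 1.282)² = 10.51.
- Pooled: n = [z_α√(2p̄(1−p̄)) + z_β√v]² / (p₁−p₂)².
- Unpooled power at 35 per arm: Φ(|p₁−p₂| / √(v/35) − z_α).

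**Step 1: reproduce 35 per group**
- Literal reading: 0.40 × (1 − 0.60) = 0.16. Unpooled, 10.51 × 0.3744 / 0.0576 = 68.3; pooled, 71.5. That is 69–72 per group two-sided and 56–59 one-sided. No variant gives 35. Power at 35 per arm is 61–64% two-sided and 73–75% one-sided, before any loss.
- Base rate 60%: 0.60 × 0.40 = 0.24. Two-sided unpooled, 10.51 × 0.4224 / 0.1296 = 34.25, rounded up to 35. The pooled form gives 38. Power at 35 is 88% pooled and 91% unpooled.
- A one-sided route also gives 35: 60% against 24%, unpooled, 27.9 rounded up to 28, and 28 / 0.8 = 35.

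**Step 2: what 60% against 24% would mean**

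If 60% is 40% users plus 20% lost, then 24% = 16% users + 8% lost. CAREs would have to cut loss by 60% as well as drug use. If loss stays at 20%, a total of 24% leaves 4% for drug use, a cut from 40% to 4%, or 90%. If CAREs cuts drug use by 60% and leaves loss alone, the comparison is 60% against 16% + 20% = 36%.

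**Step 3: put the rates on the missing-equals-positive scale**

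With loss d in each arm, unrelated to drug use, p* = p(1−d) + d. For d = 0.20: 0.40 × 0.8 + 0.2 = 0.52 and 0.16 × 0.8 + 0.2 = 0.328. The difference falls from 24 to 19.2 points, and the relative reduction from 60% to 37% (1 − 0.328/0.52). Unpooled power is Φ(0.192/√(0.470/35) − 1.960) = Φ(−0.303) = 38%.

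| Reading | Rates compared | Power at 35, two-sided | One-sided | n per arm for 90%, two-sided |
|---|---|---|---|---|
| 40% is the rate among those followed | 52% vs 32.8% | 37–38% | 49–50% | 134–138 |
| 20% added to 40%; CAREs cuts drug use only | 60% vs 36% | 52–54% | 65–66% | 86–89 |
| 60% is the rate among those followed | 68% vs 39.2% | 68–71% | 79–81% | 58–61 |
| Milder: all those lost would have been positive anyway; best case for CAREs is its 20% floor | 40% vs 20% | 45–46% | 57–59% | 106–109 |
| Milder: loss spread over time, about 10% of samples missing | 46% vs 24.4% | 47–49% | 60–62% | 98–101 |

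Ranges run from the pooled to the unpooled form.

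**Step 4: allow for repeated samples**

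The table uses one yes/no result per person, as the protocol's sample-size method does. The endpoint is a proportion of about 52 samples (2 per week × 26 weeks). With within-person correlation ρ, the variance is multiplied by (1 + 51ρ)/52: 0.313 at ρ = 0.3 and 0.706 at ρ = 0.7. These two values of ρ are assumptions. Unpooled two-sided power is then 84% and 50% for 52% vs 32.8%, 96% and 69% for 60% vs 36%, and 99% and 85% for 68% vs 39.2%. Someone lost early contributes a run of positives, which pushes ρ up.

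**The case against.** The strongest reply is that the section never calls the 20% an allowance. A reader might infer that N was inflated for dropout and the rates left alone. The text does not say so, and the only two-sided match to 35 per group found here has no inflation and appears to count the lost as positives already. That match is itself an inference, but it points the other way. Diluting 60% again to 68% would then count the loss twice, so that row applies only if 60% is the rate among those followed. This reply stands against any claim that the loss was handled as an allowance. It does not rescue the 90%, because the match relies on an unstated 60% cut in loss, while the cited effect concerns substance use.

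A reader might also conclude that the inputs contradict each other, because 20% lost sets a floor above the 16% target. That needs 20% loss in the CAREs arm. The records describe the existing programme, and CAREs sends urine-test reminders, tells social workers who missed a test, and offers a possible smartphone as a motive to comply. Lower loss in that arm is plausible. Equal loss is an assumption of this check, not a statement in the protocol.

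Finally, the planned analysis is not a binary comparison. Step 4 shows that power can be much higher on the proportion of samples, so 37–38% should not be presented as the trial's power. This stands in full.

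The pilot label does not answer the point: the protocol also declares a superiority trial and prints α and β.

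**Conclusion.** The concern holds as a defect in the stated basis for the power. The section does not define its two rates or the role of the 20%, and β = 0.10 is not shown to apply to the endpoint under the missing-equals-positive rule. By the protocol's own method, with 20% loss in each arm, two-sided power at 35 per arm is 37–38%, 52–54% or 68–71% across the three readings, and 45–49% under milder loss with the 40% base. None reaches 90%, one-sided or two-sided. Dilution is not the only shortfall: the literal 40% against 16% gives 61–64% before any loss.

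These figures assume equal loss by arm and one binary result per person. They are conservative for a proportion of samples unless results within a person are almost perfectly correlated. The documents therefore do not support saying that 90% is impossible. They support saying that it is unsubstantiated, and that it depends on assumptions about loss that are not written down.

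**What to change.** Keep N at 70 and rewrite the Sample size paragraph to:
- state the two rates on the missing-equals-positive scale of the Outcomes section;
- say what the 20% does and whether loss is assumed equal by arm; if CAREs is expected to reduce loss, state by how much;
- apply no separate dropout inflation for this endpoint, since nobody leaves the denominator;
- replace β = 0.10 with the recomputed power, or a range over the loss assumptions, and give the sidedness and formula;
- note that a one-result-per-person calculation is conservative for a proportion of samples, and that a non-significant result does not rule out the assumed 60% reduction.

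The cost is one reworded paragraph, with no added participants or procedures. The downside is a less favourable stated power.

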## Methods and analysis

### Trial design

This is a randomized controlled trial (RCT). The study uses parallel group design and is a superiority trial to explore whether the integrated rehabilitation based on CAREs promotes drug abusers to stay abstinent. The study divides participants into integrated and standardized community-based rehabilitation groups in a ratio of 1:1 and has 2 arms: the participants in integrated rehabilitation group will receive regular community-based rehabilitation plus CAREs with their matched social workers, the participants randomized to the standardized community-based rehabilitation group will only receive routine community-based rehabilitation.

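### As printed, the sample size inputs (40%, a 60% reduction, α 0.05, β 0.10, 20% loss) do not give 35 per arm, and 35 per arm does not give 90% power on them

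*Protocol article*

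**What the plan says.** All inputs are in the protocol article, Sample size. From official programme records it takes two rates: "the proportion of drug abusers in this program is around 40% and the proportion of loss-to-follow-up is 20" per cent. From the literature it takes the effect: "the use of mobile APP can result in a 60% reduction in substance use". It then reports the result: "Assuming α = 0.05, β = 0.10, a 70 participants sample size was calculated by sample size estimation for a comparison of two proportions", with 35 per group. The Allocation section repeats 35 and 35.

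The same section opens with "This is a pilot study design", while Trial design says that the study "is a superiority trial to explore whether the integrated rehabilitation based on CAREs promotes drug abusers to stay abstinent". The Outcomes section counts urine samples that are not submitted as positive. The Sample size section does not state the intervention-arm proportion, the sidedness or the formula.

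**The concern.** The section presents 70 as the output of a calculation and prints the inputs, so a reader can check it. The obvious reading is 40% positive under routine rehabilitation, cut by 60% to 16%. (The 60% must be relative, because 40% cannot fall by 60 points.) That reading does not lead to 35 per arm.

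The meaning of the 40% is also unclear. It is described as the share of drug abusers in the programme, but everyone enrolled is a drug abuser. It is equally unclear whether the 20% loss inflates the sample or is part of the failure rate.

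At stake is what a non-significant result can mean. A stated type II error of 10% lets a reader treat such a result as informative. If the error is really 39% to 48% (two-sided), it is not.

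**Working it through.** **Inputs** (Sample size section): p1 = 0.40; relative reduction 60%, so p2 = 0.40 × 0.40 = 0.16 and d = 0.24; α = 0.05; β = 0.10; loss 20%; 35 per arm, so 35 × 0.8 = 28 evaluable if the loss applies. Sidedness is not stated, so both are shown. z for α is 1.960 two-sided or 1.645 one-sided; z for β is 1.2816.

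**1. Required size for 40% versus 16%.**

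The sum of variances is V = 0.40 × 0.60 + 0.16 × 0.84 = 0.3744. The mean proportion is 0.28, so 2 × 0.28 × 0.72 = 0.4032.

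- Unpooled, n = (zα + zβ)² × V / d². Two-sided: 3.2415² × 0.3744 / 0.0576 = 68.3, so 69. One-sided: 2.9264² × 0.3744 / 0.0576 = 55.7, so 56.
- Pooled, n = (zα√0.4032 + zβ√0.3744)² / d². Two-sided: 71.5, so 72. One-sided: 58.1, so 59.

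Dividing by 0.8 for loss gives 87 to 90 randomised per arm two-sided, and 70 to 74 one-sided. Relaxing to one-sided with 80% power and no loss still needs 41 to 43 per arm. The stated 35 is not reproduced.

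**2. Power of the planned trial for 40% versus 16%.**

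Pooled: power = Φ[(d√n − zα√0.4032) / √0.3744].

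| n per arm | two-sided, pooled (unpooled) | one-sided, pooled (unpooled) |
|---|---|---|
| 35 | 61% (64%) | 73% (75%) |
| 28 | 52% (55%) | 64% (67%) |

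Exact enumeration of the two-sided chi-square test gives 62% and 53%. Fisher's exact test gives 52% and 42%. With 35 per arm, 90% two-sided pooled power needs a fall from 40% to roughly 8%, a reduction of about 80%.

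**3. Can 35 per arm be recovered?**

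Of the readings tried that keep a 60% relative reduction and 90% power, only 60% versus 24% returns it. Here V = 0.60 × 0.40 + 0.24 × 0.76 = 0.4224 and d = 0.36, so d² = 0.1296.

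- Two-sided unpooled: 3.2415² × 0.4224 / 0.1296 = 34.2, so 35, with no further allowance for loss. The pooled formula gives 38.
- One-sided unpooled: 2.9264² × 0.4224 / 0.1296 = 27.9, so 28; and 28 / 0.8 = 35 with the loss allowed for.

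Two-sided power on this contrast is 88% (pooled) to 91% (unpooled) at 35 per arm, and 80% to 83% at 28.

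**The case against.** The strongest reply is that the size can be rebuilt from the printed numbers. Both rates come from the same programme records, and missing samples count as positive. If the lost 20% are added to the 40%, the control failure rate is 60%, a 60% reduction gives 24%, and the two-sided unpooled formula gives exactly 35 per arm, with the loss already inside. A one-sided version with loss inflation also gives 35. This stands as a possible origin, so it would be wrong to say that 60% versus 24% leaves no room for loss. But neither route is written in the protocol. Each changes or combines a stated input. The first also applies the app's effect to lost participants, who are scored positive by rule; the second needs a one-sided test that is not declared.

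A second reply is that the study is a pilot. That can justify a small sample; it does not make a printed β of 0.10 true. Nor would an unseen analysis plan, since the printed inputs and result disagree with each other.

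A reader might infer several stronger things that the documents do not support:

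- *That the true power is 52% to 61%.* This holds only for 40% versus 16% with a two-sided test.
- *That a per-arm figure was entered as the total.* The 70 does resemble one (69 to 72 two-sided; 56 / 0.8 = 70 one-sided), but nothing confirms it.
- *That power is really 37%.* This comes from 0.40 × 0.8 + 0.2 = 0.52 versus 0.16 × 0.8 + 0.2 = 0.328 at 35 per arm. It assumes equal 20% loss, every lost participant wholly positive, and an effect confined to those retained. With twice-weekly tests, someone lost late is only partly positive. It is a sensitivity scenario, not a replacement figure.
- *That a null result will be reported as no effect.* The protocol does not say so; the risk lies in how a reader would use the stated power.

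**Conclusion.** The point holds for the text as printed. For 40% versus 16%, the required number evaluable is about twice the 35 per arm planned if the test is two-sided, and at least 1.6 times (56 / 35) if one-sided, before any loss. The type II error is about 39% at 35 per arm and 48% at 28 (two-sided), or 27% and 36% (one-sided), against the stated 10%.

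This rests on reading the 40% as the control positive rate and the 60% as a relative reduction. It also takes the section's own method, one proportion per arm, at face value; the repeated urine tests per participant make that an approximation. If 60% versus 24% was intended, the power claim is roughly right at 35 per arm two-sided (88% to 91%), and what is wrong is the stated control rate and the unexplained handling of loss. Either way the section needs correction.

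**What to change.** Keep 70 participants and rewrite the Sample size section so that it:

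1. says what the 40% measures, and whether the 20% loss is inside it or a separate inflation factor;
2. gives both arm proportions and the sidedness;
3. replaces β = 0.10 with the power achieved on those inputs.

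If 40% versus 16% is meant, that power is about 52% to 61% two-sided, or 64% to 73% one-sided (28 to 35 evaluable per arm, pooled). If 60% versus 24% is meant, correct the control rate and give two-sided power of about 88% to 91% at 35 per arm, or about 80% to 83% at 28 if loss is additional.

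Unless the restated power is adequate, present the comparison as a pilot estimate with a confidence interval, and state that a non-significant result will not be read as absence of effect.

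The cost is a wording amendment and, on the literal reading, a less favourable power statement. No extra participants are needed.
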